#### Acceptability and Operational Efficiency

The acceptance scores, measured as ordinal data, will be compared between the 2 screening models using the Mann-Whitney *U* test. To assess operational efficiency, the average time taken per participant for the entire screening process (efficiency assessment) and the average number of individuals screened per hour (capacity assessment) will be calculated [21]. The time taken for each station will also be assessed. Differences in procedure time and screening volume between the 2 models will be analyzed using *t* tests for mean comparisons. To provide additional insight, subgroup analyses by age and gender will be conducted to further evaluate participant acceptability. Age-based analyses will categorize participants into two groups: those aged 50 years and older, and those aged 70 years and older. Gender-based analyses will compare outcomes between male and female participants. Quantitative data related to acceptability and operational efficiency will be analyzed using R, and qualitative data will be coded and thematically analyzed using NVivo.

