### Sample Size Calculation

This study will recruit a total of 1000 participants aged 50 years and older using a 2-arm pRCT design with broad inclusion criteria based solely on age. Of these, 500 participants are targeted to have presenting VA better than 6/12 (L1), a number determined based on operational feasibility in community screenings.

Participants with presenting VA worse than 6/12 (L2) will be randomized to either the AI-assisted or traditional screening model. Sample size estimation for this randomized comparison was based on an assumed accuracy of 70% for the current traditional screening model and prevalence of 18% for any VI, 11% for disease-related VI, and 8% for refractive-error related VI (prevalence estimates were based on the SEED study) [2]. Detecting a clinically meaningful difference of 10% between the 2 screening models with 80% statistical power at a 5% 2-sided type I error requires 250 participants per arm. Therefore, a total of 500 randomized participants (L2) will be included in the primary analysis.

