##### Acceptability

In this study, acceptability is defined as patients’ perception of the AI-assisted screening model in terms of its usability, comfort, and overall satisfaction [13]. All participants randomized to either the AI-assisted or traditional screening arm will be invited to complete a structured questionnaire designed to assess their perception and satisfaction with the screening process. The questionnaire consists of 3 items rated on a 5-point Likert scale, evaluating the overall satisfaction with the screening process [14]. Five dichotomous questions are also included to evaluate factors such as awareness of AI and confidence in results. The questionnaire was developed following established psychometric principles to ensure validity and reliability in assessing patient perspectives [15].

To enhance the accuracy of data collection, trained research coordinators will administer the questionnaire with audio recording after obtaining patients’ consent. The responses will be transcribed verbatim. This approach ensures consistency in responses, minimizes misinterpretation of questions, and allows coordinators to clarify any concerns raised by participants. Missing questionnaire items will be reported as nonresponses. Given the short questionnaire and supervised administration, minimal missing data are expected. However, sensitivity analyses will be conducted if missingness exceeds 5%. Insights gained from this assessment will help refine the implementation of AI-assisted screening models and address potential barriers to patient acceptance.

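### The two age subgroups for acceptability are nested: with entry at 50, the group aged 50 and older is every randomized participant, and ages 50–69 are never examined separately

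*Protocol article*

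**What the plan says.** The subgroup plan is in the protocol article, Data Analysis Plan, under Acceptability and Operational Efficiency. It announces that "subgroup analyses by age and gender will be conducted to further evaluate participant acceptability", and then defines the age split as two groups: "those aged 50 years and older, and those aged 70 years and older". The next sentence handles gender: "Gender-based analyses will compare outcomes between male and female participants".

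The entry age is under Sample Size Calculation: "This study will recruit a total of 1000 participants aged 50 years and older". The same sentence describes "broad inclusion criteria based solely on age".

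The people who supply acceptability data are named under Acceptability: "All participants randomized to either the AI-assisted or traditional screening arm will be invited to complete a structured questionnaire". Sample Size Calculation puts their number at 500, or 250 per arm. Those with better presenting vision (L1) are not randomized and do not enter this comparison.

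No section gives the first age group an upper limit.

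**The concern.** A split into two groups should place each person in one of them. Here the lower bound of the first group is the trial's own entry age, so that group excludes nobody, and everyone aged 70 or older is in both. No group represents younger participants, so the plan as written cannot show whether younger and older people differ in how they accept the screening.

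Acceptability is a named secondary outcome and part of Aim 2, and the article says the results will be used to address barriers to patient acceptance. A real age gradient could be understated or missed, and similar results in the two groups could be read as showing that age does not matter.

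**Working it through.** The document gives no figure for the age subgroups, so there is none to reproduce. The main step is set logic; the arithmetic only sizes one of two possible readings.

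**Inputs**
- Entry age: 50 and older (Sample Size Calculation).
- Age groups: 50 and older; 70 and older (Acceptability and Operational Efficiency).
- Participants invited to the questionnaire: N = 500 randomized (Sample Size Calculation; Acceptability).
- q, the share of these aged 70 or older: not in the document. Assumed 30% to 50%.

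**Step 1, membership.** Everyone is at least 50, so the first group has n = 500. The second has n = 500q, which is 150 to 250 over the assumed range. All of these are also in the first group. The 250 to 350 people aged 50–69 appear only mixed with the older ones.

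**Step 2, reading A: arms compared within each age group.** Each test sets two separate randomized arms against each other, so each p-value is valid. The test in the first group uses exactly the data of the overall analysis and adds nothing. The test in the second group is an ordinary subgroup result. There is no result for ages 50–69.

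**Step 3, reading B: age groups compared with each other.** The mean over everyone is

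mean(all) = q × mean(70+) + (1 − q) × mean(50–69).

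Subtracting it from mean(70+) gives

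mean(70+) − mean(all) = (1 − q) × [mean(70+) − mean(50–69)].

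| q (assumed) | share of the age difference kept | share lost |
|---|---|---|
| 30% | 70% | 30% |
| 40% | 60% | 40% |
| 50% | 50% | 50% |

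**Step 4, effect on a test under reading B.** Take unit variance and a two-sample test that wrongly treats the groups as independent.
- Variance the test assumes: 1/(Nq) + 1/N = (1 + q)/(Nq).
- True variance of the contrast: (1 − q)² × [1/(Nq) + 1/(N(1 − q))] = (1 − q)/(Nq).
- Ratio of true to assumed standard error: √[(1 − q)/(1 + q)], which is 0.734, 0.655 and 0.577 for q = 30%, 40% and 50%.
- The nominal cut-off of 1.96 then acts as 1.96/0.734 = 2.67, 1.96/0.655 = 2.99 and 1.96/0.577 = 3.39 true standard errors.

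A simulation of 200,000 replicates with N = 500 agrees. The test rejects a true null about 0.8%, 0.3% and 0.06% of the time instead of 5%. For an age difference that separate groups would detect with 80% power, power is about 55%, 42% and 28%. The error is thus towards missing a difference, not towards finding a false one.

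These figures are for means under normal theory. The article treats acceptance scores as ordinal and compares them between the arms by a rank test, so Steps 3 and 4 are illustrative for that outcome.

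**The case against.** The strongest reply is that the harmful comparison is not in the text. The age sentence only categorizes; the gender sentence alone speaks of comparing the groups. The comparison stated for acceptance scores is AI-assisted versus traditional screening. On that reading no p-value is invalid: the two results are correlated and one is redundant. The attenuation figures also need a share q that the document does not give and a contrast in means that it does not specify. And this is an exploratory subgroup of a secondary outcome, plausibly a slip for 50–69.

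Most of this stands. A reader might infer that the plan commits to testing one age group against the other and that its subgroup p-values are therefore invalid. The document does not support that: such a test is suggested by the parallel gender sentence but never stated, and within-group comparisons of the arms keep their type I error. A reader might also infer that the overlap calls for an interaction model for age and for gender. It does not; male and female groups do not overlap, and the choice of subgroup model is commonly left to the analysis plan.

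The reply does not rescue the grouping. The article states the cut-points itself, so this is not a detail left to a document that is not shown. Neither reading yields a sound comparison of younger with older participants, and a slip in the wording still has to be corrected.

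**Conclusion.** The age grouping is wrong as written. This follows from the entry age and the two stated bounds and needs no assumption. Under within-group comparison of the arms, the cost is one redundant result and no result for ages 50–69. Under comparison of the age groups with each other, the cost is shared participants, a failed independence assumption and, for an assumed q of 30–50%, a loss of 30–50% of a difference in means. That size depends on q and on a comparison the article does not state, so it illustrates the error and does not measure it. The primary outcome, sample size, randomization and cost evaluation are unaffected.

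**What to change.** In Acceptability and Operational Efficiency, replace the two age groups with mutually exclusive ones: 50–69 years, and 70 years and older. This changes one phrase and needs no new data, since age is the entry criterion. The article expects statistical analysis to start in April 2026, so the correction can be made before then.

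Optional, and not required by the error: state whether the arms are to be compared within each age group or the age groups with each other, and add an arm-by-age interaction test if the question is whether the difference between arms changes with age.

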#### Cost Evaluation

A decision tree model will be employed to estimate the net costs and potential cost savings of the AI-assisted screening model compared with the traditional screening model. The model starts with a decision node for the screening method, followed by chance nodes incorporating VI prevalence and the probability of a positive or negative referral decision based on the sensitivity and specificity of each screening approach. Costs will be incorporated at the level of each screening arm to capture the resources required, including labor, equipment, and operational expenses associated with a single screening visit. Downstream costs such as treatment or follow-up are not included, as they are assumed to be equivalent across both arms and therefore do not impact the incremental cost comparison.”

Key model parameters will include VI prevalence, screening-related costs, and probability outcomes. The primary outcome will be the patient-level cost incurred under each screening model, restricted to procedures performed up to the referral decision. One-way sensitivity analyses will be conducted on key parameters to assess the robustness of the findings. The underlying hypothesis is that the AI-assisted model is at least as effective as the traditional screening model (Figure 2).

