## Abstract

**Background:**

Visual impairment (VI) affects more than 600 million people globally and significantly reduces quality of life. In Singapore, 20% of adults aged 60 years and older (~180,000 people) have VI, a figure expected to double by 2030 due to population aging. While about half of VI cases are due to uncorrected refractive errors, the rest are caused by age-related diseases. The current traditional screening model is a 2-visit, labor-intensive approach with low follow-up rates and frequent unnecessary referrals. Although AI for Disease-related Visual Impairment Screening Using Retinal Imaging, the deep learning model in this study, has demonstrated strong diagnostic performance in retrospective datasets (area under the curve=0.942), key aspects of real-world implementation such as operational efficiency, patient acceptability, workflow feasibility, and cost remain insufficiently studied. As a result, real-world evidence directly comparing artificial intelligence (AI)–assisted and traditional screening pathways is limited.

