### Hypothesis and Objectives

This study is designed as a hybrid type 1 effectiveness-implementation trial to evaluate and compare the performance, operational efficiency, acceptability, feasibility, and cost differences between the AI-assisted screening model and the traditional screening model in a community screening setting. A pragmatic randomized controlled trial (pRCT) design will be used to better represent the targeted real-world population. This study will focus on the following specific aims:

Aim 1: To evaluate and compare the referral accuracy between the AI-assisted screening model and traditional screening model for disease-related VI.

Hypothesis 1: The AI-assisted screening model will outperform the traditional screening model in detecting and referring VI cases.

Aim 2: To compare the operational efficiency and acceptability between the AI-assisted screening model and the traditional screening model, and to investigate the feasibility of the AI-assisted screening model.

Hypothesis 2: The AI-assisted screening model will demonstrate greater operational efficiency and acceptability compared to the traditional screening model and will be feasible for implementation in community-based settings.

Aim 3: To compare the overall costs of the AI-assisted screening model and the traditional screening model from a health system perspective.

Hypothesis 3: The AI-assisted screening model will be more cost-effective than the current traditional screening model from a health system perspective.

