**Figure 2. F2:**
[figure not shown]
The decision tree structure for cost evaluation. AI: artificial intelligence; Cost *C*_AI_: Total screening cost (per patient) in the AI-assisted arm. Cost *C*_Trad_: Total screening cost (per patient) in the traditional arm. *P*_0_ = VI prevalence: Probability that a participant has visual impairment. *P*_1_ = P(TP_A): Probability of true positive outcome in AI-assisted arm. *P*_2_ = P(TN_A): Probability of true negative outcome in AI-assisted arm. *P*_3_ = P(TP_T): Probability of true positive outcome in traditional arm. *P*_4_ = P(TN_T): Probability of true negative outcome in traditional arm; VI: visual impairment.

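### With one cost per arm, the cost decision tree returns only the difference in screening cost, so its sensitivity analyses on prevalence and accuracy cannot move and it does not by itself test Hypothesis 3

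*Protocol article*

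**What the plan says.** All places are in the protocol article.

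- **Data Analysis Plan, Cost Evaluation.** The tree branches on screening method, then on VI prevalence, then on the referral result as determined by sensitivity and specificity. On where costs enter: "Costs will be incorporated at the level of each screening arm to capture the resources required". On later costs: "Downstream costs such as treatment or follow-up are not included, as they are assumed to be equivalent across both arms". The outcome is cost per patient, ending at the referral decision. Prevalence, screening costs and probability outcomes are the key parameters, and one-way sensitivity analyses on key parameters are to assess robustness. The premise is that "the AI-assisted model is at least as effective as the traditional screening model".
- **Figure 2 legend.** Two costs only are defined: C_AI, described as "Total screening cost (per patient) in the AI-assisted arm", and its counterpart C_Trad. P0 is "VI prevalence: Probability that a participant has visual impairment". P1 to P4 are the true-positive and true-negative probabilities in the two arms.
- **Hypothesis and Objectives.** Aim 3 is to compare overall costs. Hypothesis 3 goes further: "The AI-assisted screening model will be more cost-effective than the current traditional screening model", from a health system perspective. Hypothesis 1 expects the AI model to be better at detecting and referring.
- **Randomization.** VI means presenting acuity worse than 6/12 in the better-seeing eye. Only participants worse than 6/12 (L2) are randomized.
- **Ground Truth Establishment.** The reference outcome is refer or not refer.

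**The concern.** A tree with chance nodes is useful only if something of value differs between its branches. Here nothing does, because each arm has a single cost and no effect measure is attached to any end point. The sensitivity analyses on prevalence and accuracy would come out flat, and a reader would take this for a robust result when it is a property of the construction.

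The reason given for omitting downstream costs also sits badly with the trial's purpose. The Abstract motivates the study by "low follow-up rates and frequent unnecessary referrals" under the traditional model, and Hypothesis 1 predicts that the arms will refer differently. If they do, the costs that follow referral will in general differ too.

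At stake is the third aim. The trial could report the AI model as more cost-effective for the health system on the strength of a difference in screening cost alone.

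**Working it through.** The document gives no cost figure, so there is none to reproduce. The check is algebra, with illustrative values marked as assumptions.

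**1. Rolling back the tree as described.** Read P1 and P2 as sensitivity and specificity in the AI arm. With cost C on every branch:

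E[C] = P0·P1·C + P0·(1 − P1)·C + (1 − P0)·P2·C + (1 − P0)·(1 − P2)·C = C

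The four branch probabilities sum to 1, so they drop out. The same holds for the traditional arm with P3 and P4.

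*Example.* Assume C_AI = 40 and C_Trad = 60 (arbitrary units). Take P0 = 0.18 (Sample Size Calculation), AI sensitivity 0.80 and specificity 0.688 (pilot figures in AI Model Development and Validation), and traditional sensitivity and specificity of 0.70 each (assumption, from the stated 70% accuracy).

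- AI: 40 × (0.144 + 0.036 + 0.56416 + 0.25584) = 40 × 1 = 40
- Traditional: 60 × (0.126 + 0.054 + 0.574 + 0.246) = 60 × 1 = 60
- Increment: −20

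Over 486 combinations (6 values of P0 from 0.08 to 1, and 3 values each of sensitivity and specificity in each arm), the increment was −20.0 every time.

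**2. Whether downstream cost can be equal under Hypothesis 1.** Put a cost r on every referred branch. The increment becomes

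(C_AI − C_Trad) + r·ΔR, where ΔR = P0·(Se_AI − Se_Trad) − (1 − P0)·(Sp_AI − Sp_Trad)

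The sample size section plans for a 10-point difference from 70%. Take sensitivity and specificity both 0.80 in the AI arm and both 0.70 in the traditional arm (assumption: the article states only overall accuracy). Then ΔR = 0.10·(2·P0 − 1).

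| P0 | ΔR | Referrals per 1000 screened, AI minus traditional | Increment if r = 100 (assumed) |
|---|---|---|---|
| 0.11 | −0.078 | −78 | −27.8 |
| 0.18 | −0.064 | −64 | −26.4 |
| 0.50 | 0 | 0 | −20.0 |
| 0.61 | +0.022 | +22 | −17.8 |
| 1.00 | +0.100 | +100 | −10.0 |

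The value 0.61 is 11/18, disease-related VI as a share of any VI on the sample size figures. In this example referral volumes are equal only at P0 = 0.50. Even there the mix differs: the AI arm has 0.50 × 0.10 = 5 per 100 more true positives and 5 per 100 fewer false positives, so treatment and follow-up need not cost the same.

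**3. P0.** If L2 is classified on the better-seeing eye, every randomized participant has VI by the article's own definition, and P0 as labelled is 1. The 18% figure describes a general population, whereas sensitivity and specificity will come from L2 participants judged refer or not refer. Neither reading matches the condition to which P1 to P4 belong. The result in step 1 does not depend on which is meant.

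**4. Cost that varies within screening.** Under Intervention Arm, only AVIRI-positive cases go to a clinical optometrist. Screening cost in that arm is therefore a fixed part plus (share AVIRI-positive) × (review cost). A single C_AI averages this out, so prevalence and accuracy have no route by which to act in the tree.

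**The case against.** Several points on the other side stand.

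- **The scope is declared.** Both Cost Evaluation sections limit costs to one visit ending at the referral decision. A narrow costing horizon is a legitimate choice. What does not stand is the reason given for it, equality between arms.
- **A reader might infer that all the sensitivity analyses are empty.** They are not. Screening costs are among the key parameters, and varying them moves the result.
- **A reader might infer that Hypothesis 3 cannot be tested at all.** That goes too far. Accuracy is compared separately under Model Performance. If the AI arm proves more accurate and also cheaper, it dominates on screening cost and no ratio is needed. That superiority result would also meet the premise of being at least as effective. The argument is made outside the tree, however, and is unavailable if superiority is not shown.
- **A reader might infer that the true-negative branches are empty.** This follows only from a literal reading of the P0 label. L2 participants whose reference outcome is not to refer will exist, so specificity can be estimated. The fault is in the label.
- **A reader might want to count false referrals in the AI arm from the pilot specificity of 0.688.** The document does not support that. The figure is for AVIRI alone in 421 retrospective images, before the optometrist makes the final decision. It served above only to show that the probabilities cancel.
- **Figure 2 is not shown.** Costs specific to each end node there would change step 1. The text and the legend give none.

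**Conclusion.** The concern holds for the tree as the text and legend describe it. The effect of prevalence, sensitivity and specificity on incremental cost is exactly zero by construction, so the planned analyses on those parameters cannot support a robustness statement. The claim that downstream costs are equivalent conflicts with Hypothesis 1. The illustration gives referral differences from −78 to +100 per 1000 screened over P0 from 0.11 to 1; it assumes equal sensitivity and specificity within each arm and shows direction and dependence, not an expected value. Aim 3 as worded can be met for screening cost, but Hypothesis 3 needs an effect measure alongside it.

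This should be fixed before analysis. It is not critical to the trial: cost is a secondary outcome, and randomization and the primary comparison are unaffected. The conclusion assumes that the unseen figure adds no branch-specific costs.

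**What to change.** Choose one of two routes before analysis, which the Results section expects to begin in April 2026.

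**Route A: make the tree do its work.**
1. Add a node for the AVIRI result in the AI arm and attach the clinical-optometrist review cost to the positive branch. Attach a referral-visit cost to the true-positive and false-positive branches of both arms, as an assumed input varied over a range that allows for non-attendance. Because this crosses the boundary set in both Cost Evaluation sections, present it at least as a sensitivity analysis and amend those sections to say so.
2. Redefine P0 as the share of L2 participants whose reference outcome is refer, estimated in the trial.
3. Report incremental cost jointly with the difference in correct-referral rate and its confidence interval, on a cost-effectiveness plane or as net benefit. A bootstrapped cost per additional correct referral is unstable when the accuracy difference is near zero.

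**Route B: narrow the claim.** Keep the single-visit boundary, but state it as a limitation of scope and not as equality between arms. Reword Hypothesis 3 to lower screening cost per participant, and drop the sensitivity analyses on prevalence and accuracy.

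**Cost.** Neither route needs new data from participants. Route A needs one assumed unit cost with a range and a little more analysis; Route B needs only rewording.
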